## Abstract

**Background:**

Adolescent idiopathic scoliosis (AIS) is the most common form of scoliosis. AIS is a three-dimensional morphological spinal deformity that affects approximately 1-3% of adolescents. Not all factors related to the etiology of AIS have yet been identified.

**Objective:**

The primary aim of this experimental protocol is to quantitatively investigate alterations in body representation in AIS, and to quantitatively and objectively track the changes in body sensorimotor representation due to treatment.

**Methods:**

Adolescent girls with a confirmed diagnosis of mild (Cobb angle: 10°-20°) or moderate (21°-35°) scoliosis as well as age and sex-matched controls will be recruited. Participants will be asked to perform a 6-min upright standing and two tasks—named target reaching and forearm bisection task. Eventually, subjects will fill in a self-report questionnaire and a computer-based test to assess body image. This evaluation will be repeated after 6 and 12 months of treatment (i.e., partial or full-time brace and physiotherapy corrective postural exercises).

**Results:**

We expect that theta brain rhythm in the central brain areas, alpha brain rhythm lateralization and body representation will change over time depending on treatment and scoliosis progression as a compensatory strategy to overcome a sensorimotor dysfunction. We also expect asymmetric activation of the trunk muscle during reaching tasks and decreased postural stability in AIS.

**Conclusions:**

Quantitatively assess the body representation at different time points during AIS treatment may provide new insights on the pathophysiology and etiology of scoliosis.

## Introduction

Adolescent idiopathic scoliosis (AIS) is the most common form of scoliosis, affecting approximately 1–3% of adolescents (10–18 years of age) [1]. AIS is a three-dimensional morphological spinal deformity that typically manifests a translation and rotation of the spine in the frontal and horizontal planes, and most of the time a reduction in the physiological curves of the rachis in the sagittal plane. AIS significantly changes the structure and appearance of the adolescent spine, thorax, and trunk [2, 3]. The severity of scoliosis is typically assessed through the Cobb angle, which is the angle between the endplates of the upper and lower end vertebrae—the vertebrae with the largest angle to the horizontal—measured from X-rays. This parameter is considered the standard method to quantify the severity of scoliosis as well as to evaluate the need for treatment, monitor the progression of the curve, and estimate the success of therapy [4]. The Scoliosis Research Society suggests that diagnosis is confirmed when the Cobb angle is greater than 10° or the axial rotation is identified [2] using the Perdriolle method [5] or the Nash and Moe method [6].

Treatment options include conservative management (bracing) or operative intervention [2]. In approximately 20% of cases, scoliosis is secondary to another pathological process, while the remaining 80% are cases of AIS [2]. Several studies on the onset and progression of AIS report a higher prevalence and severity of the curve in girls [1–3, 7]. Research is needed to identify gender-specific risk factors [7]. The cause and pathophysiology of AIS appear complex and remain unclear. To date, the causes of scoliosis have mainly been sought in congenital or acquired disorders of the vertebral structure [2]. The causes of scoliosis are supposed to be systemic disorders of, among others, mucopolysaccharide and lipoprotein synthesis [2]. On the one hand, a dysfunction of postural mechanisms involving the central nervous system (CNS) and a distorted body schema have been proposed to be part of a sequence of pathological events in the development of spinal deformity in AIS [8, 9]. On the other hand, CNS alterations have also been explored as a possible cause of AIS [3, 10–15].

CNS involvement can be studied using non-invasive brain imaging techniques such as magnetic resonance imaging (MRI), functional MRI (fMRI) and electroencephalography (EEG). MRI techniques produce detailed three-dimensional anatomical images of the brain. fMRI techniques measure small changes in blood flow that occur with brain activity, whereas EEG measures electrical brain activity. In previous studies, MRI has detected asymmetries in brainstem corticospinal bundles and significant mean volumetric differences in 22 brain regions in people with AIS. These results have led authors to suggest that anatomical alterations of the CNS may be linked to AIS [10, 11]. fMRI studies support the possibility of an underlying neurological disorder in AIS. Abnormal patterns were detected in the motor network during the execution of a simple motor task which consisted in opening and closing one’s fist [12]. A decrease in functional connectivity of cortical and subcortical motor structures was found by analyzing AIS resting-state fMRIs, acquired both during extension and semi-flexion of the lower limbs [13]. Not only MRI and fMRI studies, but also EEG studies have revealed abnormal brain activity in AIS. An increase in the amplitude of the peak in the alpha rhythm ([7.5–12.5] Hz) was found in the central, frontal, parietal, and occipital regions when comparing brain activity of adolescents with AIS with that of healthy controls during upright standing posture [14]. Differences in electrocortical dynamics were found between girls with AIS and controls performing a balance task that involved alteration of ankle proprioception. Specifically, a significant suppression in the power of the alpha ([8–12] Hz) and beta ([13–30] Hz) bands emerged in the AIS group during the ankle vibration interval with eyes open and a significant increase in theta ([4–7] Hz) band power with eyes closed [15]. Alpha oscillations are a marker of the excitability of the somatosensory cortex. Suppression of alpha, compared to baseline, indicates somatosensory cortical activation. Theta rhythm, also involved in balance control, intensifies when control demands increase. EEG data acquired in four different standing positions in adolescent girls with AIS revealed a significant increase in theta activity and lateralized alpha activity during all balance tasks [3].

Parallel to the study of CNS response through non-invasive brain imaging techniques in AIS, human motion analysis provides insight on the quality of balance and movement. Marker-based stereophotogrammetry, inertial measurement sensors, surface electromyography (sEMG) sensors, and force plates, among other systems, can provide valuable information on joint kinematics, muscle activation, center of mass (COM), and center of pressure (COP) displacement. Balance control measured through force plates revealed no differences between girls with AIS and CTRL in a standing upright position [3, 14, 16, 17]. Differences between girls with AIS and CTRL have been detected when the experimenters asked the participants to stand upright while either raising their arms with eyes closed or during sensory cues alteration (i.e., ankle tendon vibration or galvanic vestibular stimulation) [3, 14, 16].

Quantifying EEG, sEMG and motion patterns before, during and after bracing and physiotherapy treatment could be a first step to clarify what triggers the lateral spinal curvature that produces asymmetric loading of the skeletally immature spine, which, in turn, causes asymmetric growth and a progressive wedging deformity [18].

Last but not least, body representation alterations, i.e., alterations in both the *body schema* and the *body image*, need to be better understood in this clinical population. *Body schema* refers to the position and configuration of the human body as a 3-dimensional object in space. The body schema is the sensorimotor representation of the body used to plan and execute movements [9, 19–21]. Alterations of body schema have been proposed to parallel the development of spinal deformity in AIS [8]. *Body image* is a complex psychological construct that encompasses different dimensions, namely perception, cognition, affect, and behavior [22]. Body image refers to the disfiguring appearance caused by scoliosis spinal deformities, and the related brace treatments. Altered body image has a notable impact on the mental health of adolescents [23], which has detrimental effects both on quality of life and adherence to treatment [24, 25].

Body schema is generally assessed using self-reported assessment scales [26]. We propose two ad-hoc tasks to monitor it in a longitudinal study. (i) The *forearm bisection task* is a simple and common test widely used in clinical and research fields to investigate the body schema [27]. It requires the subjects to point to the perceived midpoint of their forearm. Since AIS significantly changes the structure of the adolescent spine, thorax, and trunk, we include an innovative task that involves the movement of the trunk. (ii) The *target reaching* forces the subjects to perform forward trunk movements. It aims to investigate the body schema in adolescent girls with AIS and to determine if alterations in the body schema can modify the planning of movement within the action space immediately surrounding the body, also known as the peripersonal space. The outcomes of the target reaching will be compared with those resulting from the standardized forearm bisection task, to ensure its reliability as a task to evaluate the body schema in adolescents with AIS. During these two tasks, the performance of the subjects will be quantitatively assessed using EEG, marker-based stereophotogrammetry, IMUs, sEMG, and force plates. The EEG signal allows us to quantitatively record the activation of the sensorimotor cortex where the body schema is ‘dynamically’ represented. In fact, the representation of the body schema is plastic and can vary [27]. Marker-based stereophotogrammetry will allow us to accurately estimate the timing of each movement and to relate IMU, sEMG and force plate signals with the EEG.

Body image has been largely neglected in clinical practice and is generally assessed with self-reported questionnaires, which are not capable of detecting the complexity of body image alterations. We propose (i) a self-reported questionnaire and (ii) a computer-based test to investigate body image alterations.

Taking into account the results of the state-of-art literature, the primary objective of this experimental protocol is to quantitatively investigate alterations of body representation in AIS. We believe that a quantitative evaluation of body representation alterations in AIS in a longitudinal study may provide new information to better understand the pathophysiology and etiology of scoliosis. The novelty of our study is also based on including the evaluation of girls with AIS before any treatment. We cannot exclude a priori that altered brain activations of the sensorimotor network, altered body schema and image, increased attention toward shoulders and back could be a consequence of treatment per se. Physical therapy exercises and brace treatment could increase proprioception and awareness of the shoulder and back muscles. Our longitudinal study aims to rule out the hypothesis described above.

Results from our previous study, conducted on subjects with AIS who underwent brace treatment, [3] revealed: (i) a significant increase in relative power of EEG delta ([1–4] Hz) and theta rhythms, compared to controls, located in central areas; a significant increase in the laterality index in alpha range observed in adolescents with AIS with main right curve, demonstrating an imbalance between the two sensorimotor areas; (ii) no differences in balance performances between groups; (iii) no differences between controls and adolescents with AIS for the single body segment. However, the investigation of body schema revealed possible alterations in the overall representation of the trunk, namely in the perception of the shoulders-waist proportion, and in its inclination. Based on the literature background and our previous work [3], we expect that, compared to controls, adolescents with AIS, before any treatment, will show: (i) altered brain activation of the sensorimotor network; (ii) greater sway, unbalanced activation of muscles on the right and left sides of the back, and more variable IMU signals on the frontal plane when performing the target reaching, as a result of less efficient control of their balance on the plane with the larger scoliotic deformity; (iii) altered body schema reflecting altered activation of the sensorimotor network.

## Materials and methods

### Experimental design

Adolescent girls with a confirmed diagnosis of mild (Cobb angle ranging from 10° to 20°, no spine surgery) and moderate (Cobb angle ranging from 21° to 35°, no spine surgery) scoliosis (AIS) will be enrolled at the Adolescence Spine Diseases Diagnostic and Therapeutic Center of the Padova University Hospital. Subjects matched in sex and age without AIS—controls (CTRL)—will be recruited through flyers posted in middle and high schools in Padova.

Adolescent girls with AIS and controls will undergo a three-phase experimental protocol (T0, T1, T2).

This longitudinal study aims to follow and quantify alteration in body representation in parallel to the progression of scoliosis from the time of the first diagnosis by the physiatrist (T0) and up to one year after diagnosis (T1, T2). At T0, subjects (AIS and CTRL) will undergo two tasks aimed at investigating possible alterations in *body schema* representation. During the experiment, we will use EEG to record changes in brain oscillations; sEMG to assess possible imbalances in muscle activation, IMUs, motion capture, and force platforms to monitor the performance and movement characteristics during the balance and motor tasks. A self-reported questionnaire and a computer-based test will be administered to all subjects to investigate *body image* alterations in AIS.

After this evaluation (T0), if the adolescent shows low-grade scoliosis, an expert physiotherapist gives her corrective postural exercises to perform daily (30 min / day) until growth is complete. Participants’ performance in scoliosis-specific exercise will be monitored by the physiotherapist at least once a week. The set of exercises is believed to improve postural awareness, proprioception, and ability to dissociate the movements of the lumbar spine from the thoracic one in the different planes of space. Treatment will be planned in the individual patient, based on the dysfunction detected in the clinical assessment. When scoliosis exceeds the 20°Cobb and there is evidence of progression risk, a rigid partial (18 hours/day) or full-time brace (23 hours/day) is also prescribed.

The same physical, neurological, and cognitive evaluations of T0 will be repeated after 6 (T1) and 12 months (T2) of therapy in AIS and after 12 months (T2) in CTRL. A team of bioengineers, physiatrists and physiotherapists will perform the experimental protocol to ensure the comfort of the subjects and the quality of the data (Fig 1).

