To reveal possible alterations in body image representation in adolescent girls with AIS, BUT sub-scores will be calculated (scoring instructions are reported in S1 Appendix). Response accuracy (i.e., percentage number of correct responses over the total number of trials) and reaction times (RTs), collected as outcome variables during the Computerized body self-recognition task, trials will be clustered according to the target stimulus and subsequently analysed. The correlations between the BUT questionnaire subscores and RTs and accuracy will be assessed using the Pearson’s correlation coefficient (r).

The results of AIS-adolescent girls and controls of the same age and sex will be compared by statistical analyses. Shapiro-Wilk normality test will be applied on all the data collected to check the normal distribution. A two-tailed paired sample t-test or a two-sided Wilcoxon rank sum test (*p* < 0.05) will identify differences between the two groups (AIS vs. CTRL) and between the three time points evaluation (T1, T0 and T2) after having run a global test (either repeated measure ANOVA, or Friedman test depending on data normality).

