Body schema refers to the sensorimotor body representation that entails tracking and updating the position and configuration of both body parts and other objects in space towards which reaching movements can be planned [27]. The functional representation of the action space immediately surrounding the body, also known as the peripersonal space, usually undergoes changes concurrent with body schema alterations. Through the target reaching we will assess if possible body schema alterations in adolescent girls with AIS can alter the planning of the movement within the peripersonal space. The forearm bisection task is a simple and common test widely used in clinical and research fields to investigate the body schema [27]. We will use this task to test whether adolescent girls with AIS have a different representation of the metric properties of their own body compared to CTRL. By replicating the same tasks at time T1 and T2, we will test how the body schema will change as a function of control postural exercises or the effectiveness of brace therapy. The first test of the body schema (T0) is expected to highlight a possible alteration in the perception of the shoulders-waist proportion and in the inclination of the trunk. We expect a decrease in alteration in their body representation due to the treatment. The two tasks are designed to reveal body schema alterations at T0 in the AIS group, which should improve significantly after the 6 month exercise and brace-treatment period (T1).

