Cognitive and behavioral assessment will investigate two aspects of body image perception: how subjects perceive their body appearance and the emotional and cognitive aspects of body [26]. We expect to find significant differences between the AIS group compared to CTRL at T0, with AIS having a worse self-attitude towards body image (i.e. body image dissatisfaction). Worst score in the sub-domains of global severity index, body image concerns, avoidance and compulsive self-behaviors (BUT-A), and specific higher concerns for shoulders, chest, and hips than other body parts (BUT-B). Second, we expect to find body attentional bias in the AIS group towards disease-specific body parts (shoulders, back), meaning faster reaction time and higher accuracy in response to disease-relevant images, and particularly to own body-relevant images. At T1, we expect to find a significant improvement in self-attitude scores for body image compared to T0 and a reduction of the attentional bias towards disease-relevant body parts, which means no differences in reaction time and accuracy between relevant and irrelevant body parts.

A risk of the proposed experimental protocol is boredom and loss of interest and compliance due to its duration (circa 80 min) and complexity. If necessary, the protocol can be divided into three separate sessions on three different days. Block (i), blocks (iii-iv), and block (v) of the protocol are independent and investigate different research questions. Another possible risk is related to the longitudinal design. Adolescent girls with AIS may not be available to repeat neurophysiological, postural, and cognitive assessment after 6 and 12 months. To mitigate this risk, we will make our best efforts to retain subjects through periodic follow up; and we will increase the number of recruited individuals at T0 to take into account an approximately 20% dropout rate. Although not all individuals may complete all follow-up sessions, the protocol will still provide valuable data that will allow us to investigate the muscular and neurophysiological correlates of AIS compared to CTRL at enrollment (T0). The forearm bisection task, block (iv), and resting-state EEG recording can still provide us significant information regarding possible body schema alterations, neurophysiological patterns, and postural performances.

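### Controls appear to have no 6-month visit and no between-group comparison of change is stated, so improvement in AIS girls cannot be attributed to treatment

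*Protocol article*

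**What the plan says.** **Visits.** Two sentences in Experimental design differ. The general one reads "Adolescent girls with AIS and controls will undergo a three-phase experimental protocol (T0, T1, T2". The one that sets out the repeat evaluations by group has them "after 6 (T1) and 12 months (T2) of therapy in AIS and after 12 months (T2) in CTRL". The caption of Fig 1 says the figure tabulates what is recorded for each group and phase, but the figure is not available here.

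**Aim and expectations.** The Objective in the Abstract includes to "track the changes in body sensorimotor representation due to treatment". The Discussion says "We expect a decrease in alteration in their body representation due to the treatment" and expects body-schema alterations "which should improve significantly after the 6 month exercise and brace-treatment period (T1". On body image it says "At T1, we expect to find a significant improvement in self-attitude scores for body image compared to T0". It also expects a reduced attentional bias at T1, "which means no differences in reaction time and accuracy between relevant and irrelevant body parts".

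**Analysis.** Foreseen data processing names two families of comparison at p < 0.05, AIS against CTRL and between the three time points, "after having run a global test (either repeated measure ANOVA, or Friedman test depending on data normality". It mentions no group-by-time term and no comparison of change between groups.

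**Size.** Procedure expects data from 15 AIS girls and 15 controls.

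**The concern.** The participants are girls aged 11 to 16 who repeat the same reaching, bisection and reaction-time tasks every six months. Scores can move through familiarity with the tasks or through normal growth, with no help from treatment. A control group measured at the same visits is the design's means of removing those two sources.

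On the group-specific visit sentence, that means is missing at T1, the visit at which the body-schema and body-image improvements are expected. At T2 control data exist, but the stated analysis does not say that change will be compared between groups. Followed as written, the plan could report a practice or maturation effect as a response to brace and exercise.

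**Working it through.** **1. Which comparisons the visit schedule allows.** Taking the group-specific sentence at its word:

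| Visit | AIS | CTRL | Task exposures by then (AIS / CTRL) |
|---|---|---|---|
| T0 | yes | yes | 1 / 1 |
| T1 | yes | no | 2 / 1 |
| T2 | yes | yes | 3 / 2 |

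- T0–T1 change can be estimated in AIS only.
- T0–T2 change can be compared between groups, with unequal exposure.
- A three-visit test cannot include controls, because their T1 cell is empty.
- The Friedman test has no group factor in any case.
- A repeated-measures ANOVA with a group factor on T0 and T2 could compare change, but none is stated.

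**2. Inputs.** From the documents: n = 15 per group and two-sided 5% (Procedure; Foreseen data processing). The stated numbers are roughly consistent with each other: 40 × 0.8 = 32 against 30 expected, and 30 / 0.8 = 37.5, so 38, against 40 recruited. The effect size behind 15 per group is not given, so that figure cannot be reproduced. The shift g (in baseline SD) and the T0–T1 correlation r below are assumptions, shown as a range.

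**3. How often the AIS-only test is significant when treatment does nothing.** The standardised paired effect is dz = g / √(2(1 − r)). Power is from the noncentral t with 14 df and noncentrality dz × √15. Example: g = 0.5 and r = 0.5 give dz = 0.5 / √1 = 0.5 and noncentrality 1.94, hence 44%.

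| Shift g | r = 0.5 | r = 0.7 | r = 0.8 |
|---|---|---|---|
| 0.2 SD | 11% | 15% | 21% |
| 0.3 SD | 19% | 29% | 40% |
| 0.5 SD | 44% | 64% | 81% |

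Simulation with 20,000 runs at three of these settings gave 43.6% (0.5 SD, r = 0.5), 29.3% (0.3 SD, r = 0.7) and 64.4% (0.5 SD, r = 0.7), in agreement.

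**4. With the global test first.** The table ignores the plan's condition that pairwise tests follow a global test. Simulating a three-visit ANOVA in AIS as that condition, with the same shift at T1 and T2, gives about 7–14%, 13–32% and 36–77% for the three shifts over r = 0.5 to 0.8.

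**5. What a between-group comparison of change does.** A shift common to both groups cancels. At the same three settings, a t-test on change scores, 15 against 15, rejected in 4.9–5.0% of runs.

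Its precision is limited. The two-sample t-test with 15 per group has 80% power at a standardised difference of 1.06. In baseline SD the detectable difference in change is 1.06 × √(2(1 − r)):
- r = 0.5: 1.06 × 1.00 = 1.06
- r = 0.7: 1.06 × 0.775 = 0.82
- r = 0.8: 1.06 × 0.632 = 0.67

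**6. Unequal exposure at T2.** If the third exposure gives AIS girls an extra practice gain of 0.1 to 0.3 SD, the false-positive rate of the T0–T2 comparison rises from 5% to 6–13% (r = 0.5) or 6–18% (r = 0.7). This is smaller than the inflation in step 3 but needs stating.

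**The case against.** Several points on the other side are fair.

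- **The two visit sentences may not truly conflict.** The first may be a general introduction and the second the schedule, with Fig 1 settling it. That stands as far as it goes, and the request is only to reconcile them. If the second sentence is the schedule, the T1 problem is confirmed.
- **An article may leave model terms to a fuller document.** True of fine detail. Here, however, the article names its tests and comparisons, and none of them answers an aim framed as change caused by treatment.
- **A reader might infer that the plan can never compare the groups over time.** The documents do not support that: control data exist at T2, and an ANOVA with a group factor could use them.
- **A reader might infer that every longitudinal hypothesis sits at T1.** The Discussion also expects EEG changes after 12 months, and the sample size rests on a cross-sectional EEG difference.
- **A reader might infer that a non-significant difference at T1 is a formal rule for declaring the attentional bias reduced.** The sentence is an expectation in the Discussion. The analysis section adopts no such rule, so no error rate should be attached to it. The narrower point stands: absence of a difference at T1 does not show a reduction.
- **The 0.5 SD shift has no source in the documents.** Agreed. It is the top of an assumed range, and the 0.2 and 0.3 SD rows deserve equal weight.

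**Conclusion.** The concern holds in limited form. If controls miss T1, no analysis can separate the 6-month change in AIS girls from practice or maturation, and the stated tests do not use the T2 control data to compare change. Under no treatment effect the AIS-only paired test exceeds its nominal 5% at every assumed shift: from 11% (0.2 SD, r = 0.5) to 81% (0.5 SD, r = 0.8), and from about 7% to about 77% once a significant global test is required first. These rates depend on the assumed shift and correlation, which the documents do not give. That the comparison is uncontrolled depends only on the visit schedule.

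It would be too strong to conclude that adding controls at T1, or comparing change at T2, would isolate the effect of treatment. The controls are healthy and there is no untreated AIS group. They address practice and normal maturation, but not the natural course of scoliosis or regression to the mean. Causal wording is therefore unsupported at T2 as well as at T1.

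**What to change.** 1. Reconcile the two sentences in Experimental design with each other and with Fig 1, so that the control visits are unambiguous.
2. Name the group × (T2−T0) contrast as the main longitudinal comparison. One suitable source is a mixed model with group, visit and group × visit, using all available visits. Report it with a confidence interval. Do not call it confirmatory: 15 per group detects only about a 0.7 to 1.1 SD difference in change (r = 0.8 to 0.5).
3. State that by T2 AIS girls have had three task exposures and controls two.
4. Report T0–T1 change as AIS-only and descriptive.
5. In the Objective and Discussion, describe change as observed during treatment, not as caused by it, at both T1 and T2.
6. For attentional bias, estimate the T0–T1 change in the relevant-minus-irrelevant score with a confidence interval, and do not read the absence of a difference at T1 as a reduction.

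**Cost.** Changes to wording and analysis only, on data already planned. The price is a more modest claim at T1 and T2.
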